Each of the CPRs will subsequently be augmented by integrating interaction effects. This purports to better accommodate for the fact that a given feature may be more impactful in the presence of one of its counterparts. Mean (and not mean *absolute*) SHAP interaction values will be used in order to distinguish between synergistic and redundant interactions. The decile rank of each of the twenty-eight mean SHAP interaction values from each model will be calculated. A dot plot will be provided to visualise each feature-pair’s mean SHAP interaction value relative to other pairs. (We speak of twenty-eight mean SHAP interaction values because there are eight features, and (*i*, *j*)- and (*j*, *i*)-values capture the same interaction effect, while (*k*, *k*)-values capture main effects and were the object of the above paragraph). Dealing with a large number of feature-pairs, we will use stringent percentiles in selecting interaction effects for inclusion. The 90th percentile of the sample of twenty-eight mean SHAP interaction values will be computed. Feature-pairs with mean SHAP values above this threshold will be selected as the most important synergisms. Feature-pair selection will also incorporate domain knowledge, as some feature-pairs have well-established synergisms that may merit inclusion even if they fall somewhat short of the 90th percentile cutoff. Examples include CHF and age [121], hypertension and age [122], and hypertension and DM [123]. Selected feature-pairs will be integrated into the CPRs as accompanying rules: ‘if both feature *i* and *j* of the pair are present in the patient, add one additional point to the patient’s total score’. To mitigate overfitting, we will cap the number of points that can be added to accommodate synergisms to three. We will further cap the number of interaction pairs retained at a maximum of three. The augmented CPRs will be summarised in tabular form and their acronyms labelled with an asterisk (e.g., CHA_2_DS_2_-VASc*). A worked example of the CPR development process here described can be found in Appendix S6 in Supplementary Materials file S3.

Both non-augmented and augmented CPRs will undergo evaluation. See “CPR Evaluation”.

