Primary: Does the acute context of AFAIS, and the importance of the index event, call for a CPR bespoke to early secondary prevention? In other words, are the main effects of the constituent features of CHA_2_DS_2_-VASc different post-stroke? Besides main effects, are there synergistic or other non-linear interaction effects between stroke history and the constituent features of CHA_2_DS_2_-VASc that can further improve prediction of 90-day AFAIS recurrence? Secondary: How do CPRs trained to capture 90-day AFAIS recurrence perform with regard to secondary outcomes (7-day recurrence, 7- and 90-day HT, 90-day decline in functional status, and 90-day all-cause mortality)? Exploratory: How do CPRs trained to capture 90-day AFAIS recurrence perform with regard to recurrence among non-AF AIS patients?	Primary: LR and XGBoost can capture the main effects of the constituent features of CHA_2_DS_2_-VASc in the context of secondary prevention. XGBoost is also equipped to capture complex functional relationships between the features. The outputs of these models can be employed to construct CPRs that outperform CHA_2_DS_2_-VASc for predicting 90-day recurrence in AFAIS patients. Specifically, fair (AUC < 0.8) to good (< 0.9) discrimination can be achieved for this high-risk group, alongside improved calibration and clinical utility relative to CHA_2_DS_2_-VASc. Secondary: The resulting CPRs also outperform CHA_2_DS_2_-VASc for predicting secondary outcomes.	LR and XGBoost models: Discrimination assessed using AUC and calibration curves. Calibration assessed using calibration curves, slopes, and Brier scores. Additional metrics: F1 score, accuracy, precision, sensitivity, specificity, Youden index, PPV, NPR, PLR, NLR. Resulting CPRs: Discrimination assessed using AUC and calibration curves. Calibration assessed using calibration curves, slopes, and Brier scores. Clinical utility assessed via DCA relative to default strategies as well as CHA_2_DS_2_-VASc. Test tradeoff analysis will be used to balance ease-of-use with clinical utility.	Primary: LR—680 patients deemed necessary, see Appendix S5.3 in Supplementary Materials file S3. XGBoost—learning curve analysis and KL divergence will afford post hoc insight on suitability of sample size. 75% of AF dataset will be used, comprising 2072 AFAIS patients. Remaining 25% (691 patients) will be withheld as test set. Secondary: Entire AF dataset will be used, comprising 2763 AFAIS patients. Exploratory: Entire non-AF dataset will be used as supplementary test set, comprising 7809 AIS patients.	Models will be instantiated (LR with L2 regularisation and XGBoost with default hyperparameters) on AF dataset, randomly split into training (***T***, 75%) and test sets (***t***, 25%), preserving distribution of outcomes. Nested cross-validation (5 × 2) will be employed for training and hyperparameter tuning. After hyperparameters are optimised, final models will be retrained using the entire training set. The test set ***t*** will then be used for evaluation of final LR and XGBoost models, focusing on discrimination and calibration. Feature importance will be reported via coefficients and odds ratios (ORs) for LR and feature gain for XGBoost. To derive CPRs from these models, SHAP will quantify both main effects and interaction effects of predictor variables. Main effects, represented by mean SHAP values, will be used to rank and assign scores to each predictor, enabling the creation of interpretable and clinically applicable CPRs. Interaction effects, captured through SHAP interaction values, will further refine our CPRs by identifying significant synergistic or redundant relationships between predictors. These interactions will be incorporated into so-called ‘augmented CPRs’ in the form of accompanying rules. Both non-augmented and augmented CPRs will be evaluated on the test set ***t*** in terms of discrimination, calibration, and clinical utility. Clinical utility will be measured using NB via DCA, plotting NB against risk thresholds within the 0.01–0.20 range. The CPRs will be compared on the basis of clinical utility to one another, CHA_2_DS_2_-VASc, and default strategies (‘treat all’ and ‘treat none’). Test tradeoff analysis will evaluate whether any incremental benefit in clinical utility observed with augmented CPRs justifies the added complexity of incorporating accompanying rules. Secondary: CPRs (and not models) will be evaluated on the entire AF dataset for each secondary outcome via discrimination, calibration, and clinical utility. Exploratory: CPRs (and not models) will be evaluated on the entire non-AF cohort to assess generalisability and compare their clinical utility when applied to an unseen yet closely related patient population.	Discrimination will be classified as follows [101]: AUC of 0.81–0.90 = good, 0.71–0.80 = fair, 0.61–0.70 = modest, and 0.51–0.60 = poor. Miscalibration is detrimental to medical decision making and poor calibration has been coined the Achilles heel for CPR applicability [102]. As such, we consider at least as important as discrimination and give precedence to clinical utility, which provides a more comprehensive evaluation by integrating both discrimination and calibration when interpreting the performance of our CPRs. CPRs will be considered clinically useful at a given risk threshold only if their NBs exceed those of both default strategies. Of those deemed useful, we will rank the CPRs (including CHA_2_DS_2_-VASc) based on NB across the 0.01–0.20 risk thresholds. Test tradeoff (∆*N**B*) will be interpreted only insofar as spotlighting those CPRs which would be more conveniently deployable without sacrificing significant clinical utility.

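### The sign of the mean SHAP interaction value depends on how the two features are correlated, so it does not reliably separate synergy from redundancy in the augmented CPRs

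*Protocol article*

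**What the plan says.** Under CPR Development in Section 2.12.6, each CPR is extended with interaction rules. The signed mean is chosen over the absolute mean for one stated purpose: "SHAP interaction values will be used in order to distinguish between synergistic and redundant interactions". The number of candidates is explained: "We speak of twenty-eight mean SHAP interaction values because there are eight features". The 90th percentile of these values is the cut-off: "Feature-pairs with mean SHAP values above this threshold will be selected as the most important synergisms". For each selected pair, a patient with both features present gets a bonus: "add one additional point to the patient"'s total. There is a second way in: "Feature-pair selection will also incorporate domain knowledge, as some feature-pairs have well-established synergisms", which may be included even if they fall somewhat short of the cut-off. There is also a limit: "We will further cap the number of interaction pairs retained at a maximum of three".

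Tables 3 and 4 describe the same step as "identifying significant synergistic or redundant relationships between predictors", and then say that these interactions enter the augmented CPRs as rules.

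**The concern.** SHAP values are centred on the average prediction of a reference population. A signed mean of a centred quantity need not carry the sign of the effect behind it. If the mean instead follows the correlation between the two features, the rule selects pairs partly by how the comorbidities cluster in the cohort, not by whether they act together on recurrence.

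The bonus points depend on this. Whether interactions improve prediction of 90-day recurrence is part of the primary updating question in Table 3, and the augmented CPRs compete in the final net-benefit ranking. A wrongly signed pair would give an extra point to patients whose joint risk is lower than the main effects imply, and a real synergy could go unused.

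**Working it through.** **The plan's own figure.** Eight features give 8 × 7 / 2 = 28 pairs, as stated. With linear interpolation, the 90th percentile of 28 distinct values leaves 3 above it, which matches the cap of three.

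**Inputs not in the article.** The SHAP variant, background data, output scale, feature covariances and effect sizes are not given. They are assumed below and varied.

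**Derivation.** Let the log-odds be f = b0 + b1·x1 + b2·x2 + g·x1·x2 for binary features with prevalences p1 and p2. For interventional SHAP with a population background, the interaction of the pair in one patient is

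v(1,2) − v(1) − v(2) + v(∅) = g·[x1·x2 − p2·x1 − p1·x2 + E(x1·x2)].

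Averaged over patients:

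g·[E(x1·x2) − p1·p2 − p1·p2 + E(x1·x2)] = 2g·Cov(x1, x2).

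This is the pair total. Each of the two off-diagonal entries holds half, g·Cov.

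**Numbers.** Assume p1 = 0.70, p2 = 0.25 and g = +0.8. The product of the standard deviations is √(0.70 × 0.30 × 0.25 × 0.75) = 0.1984. At correlation −0.3 the covariance is −0.0595, and g·Cov = 0.8 × (−0.0595) = −0.0476. Exact enumeration gives, per matrix entry:

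| Correlation | Interventional | Path-dependent (one two-split tree) | Conditional | All-zero reference |
|---|---|---|---|---|
| −0.3 | −0.0476 | −0.0238 | 0 | +0.0462 |
| 0 | 0 | 0 | 0 | +0.0700 |
| +0.3 | +0.0476 | +0.0238 | 0 | +0.0938 |

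With g = −0.8 every non-zero entry changes sign. At correlation −0.3 the antagonistic pair therefore scores +0.0476 and the synergistic pair −0.0476.

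**Probability scale.** With an intercept of −2.2 and main effects of 0.3, at correlation −0.3 and g = +0.8, the interventional mean is −0.0089, although the interaction on that scale is +0.150.

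**Higher-order terms.** With four features and a three-way term of 0.4, exact equality is lost: 0.0241 against g·Cov = 0.0222 in one example, and +0.0003 against −0.0020 in another. Table 2 allows XGBoost depths of 3 to 9, so such terms are possible.

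**Uncorrelated pair in finite samples.** With g = 0.8, 2072 background and 691 test patients, 2000 simulations gave a mean of −0.0001 (SD 0.0036), negative in 52%. A weak interaction of 0.1 at correlation +0.3 scores 0.1 × 0.0595 = +0.0060 and would usually outrank it.

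**A plausible-looking pair.** Assume vascular disease in 38% of men and 22% of women, with 45% women. Cov = 0.45 × 0.55 × (0.22 − 0.38) = −0.0396, a correlation of −0.17. An interaction odds ratio of 2 (g = 0.693) gives a pair total of 2 × 0.693 × (−0.0396) = −0.0549. An odds ratio of 0.5 gives +0.0549.

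**Fitted models, as illustration.** XGBoost was simulated at depth 3 with 100 trees, 2072 training patients, recurrence of about 10%, the age pair removed, and 40 to 100 runs per scenario. Prevalences and effects were assumed.
- Correlation about −0.18: a true synergy (odds ratio 2) reached the top three in 0% to 2% of runs. A true redundancy (odds ratio 0.5) was selected in 93% to 97.5%. Class weighting did not change the pattern.
- Uncorrelated: synergy was selected in 35% to 52%, and redundancy in 27.5% where tried. Random choice of 3 of 27 pairs would give 11%. Both exceed chance because a large effect of either sign inflates whatever covariance the sample happens to show.
- Correlation +0.18: synergy was selected in 95%, redundancy never.
- Ranking by the log-odds double difference: synergy was selected in 69% to 70% of unweighted runs at correlation −0.18 or 0, and in 60% of class-weighted runs at −0.18. Redundancy was selected in 0% at −0.18.

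**The case against.** The strongest reply is about scope, and much of it stands. Exact equality with interaction times covariance needs interventional SHAP, the evaluated population as background and purely pairwise terms, none of which the article fixes. An all-zero reference would keep the right sign. For positively correlated pairs the rule works. The LR model has no product terms described, so on the log-odds scale it has no interaction to missign. The simulations cover XGBoost at one depth, and the MLP was not simulated. The only negative covariance certain from the document is that of the two age indicators, which are mutually exclusive and could never trigger a both-present rule anyway.

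It can also be said that safeguards exist: domain knowledge, the cap of three, and evaluation of augmented and non-augmented CPRs side by side on net benefit. These limit the damage but do not correct the direction. The domain-knowledge clause can add pairs and has no provision for removing wrongly signed ones. The cap limits how many pairs enter, not which. The net-benefit comparison may expose a poor CPR but cannot recover a synergy that was never selected.

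The worked example in Appendix S6 is not shown. It might state the reference used, but the text as published gives the signed mean a meaning that it does not have in general.

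**Conclusion.** The point holds in a limited form. Under the usual population background, the signed mean tracks the interaction effect times the feature covariance, or is zero under conditional SHAP. Its sign is right for positively correlated pairs, uninformative for uncorrelated ones and reversed for negatively correlated ones. Following the stated rule can therefore miss a true synergy and award a point to an antagonistic pair in the XGBoost- and MLP-based augmented CPRs.

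A reader might infer that the rule never separates the two, that the mean always equals effect times covariance, or that the simulated selection rates predict what will happen in VISTA. The document supports none of these: the SHAP variant and background are open, no covariances are given, and the rates rest on assumed prevalences. How many of the 28 pairs would be affected is unknown.

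There is also a smaller mismatch. Tables 3 and 4 say that synergistic or redundant interactions become rules, while CPR Development only ever adds points, so redundancy has no way in.

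Because the non-augmented CPRs are unaffected and the augmented ones are compared with them, this should be fixed but does not undermine the study as a whole.

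**What to change.** In CPR Development, replace the signed mean SHAP interaction value as the ranking quantity with a contrast that keeps its sign: the double difference of the model's log-odds, f(1,1) − f(1,0) − f(0,1) + f(0,0), averaged over the other features in the training set T. Accept as synergisms only pairs with a positive value. Leave out the pair formed by the two age bands; with 27 distinct values the 90th percentile still leaves three above it. Where one member of a pair is an age band, set the age indicators together so that no impossible age pattern is scored.

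In Tables 3 and 4, bring the description into line with the rule, for example by dropping the reference to redundant relationships. A rule that subtracts points for redundant pairs would also resolve the mismatch, but that is the authors' choice and is not needed here.

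The cost is a few sentences, plus predictions on at most 2^8 = 256 feature patterns per model. No model is refitted and no further data are needed. The change should be made before results are seen.

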##### Global Interpretation

To summarise the average impact of each feature on our models’ outputs across the test set, we will calculate mean absolute SHAP values. The absolute mean will also be taken across SHAP interaction values. SHAP summary plots will be provided: bar plots to depict mean absolute SHAP values, and beeswarm plots to depict the distribution of local SHAP values in order to intuitively understand variability. We will also provide 8 × 8 beeswarm plots which depict interaction effects in the off-diagonal entries of the feature grid, 28 of which are unique owing to the symmetry of SHAP interaction values.

SAGE values will be reported with regard to the AUC and graphically represented using bar plots. Unlike SHAP, the SAGE algorithm readily provides the standard error of each feature’s importance. These will be utilised to gauge the stability of the importance estimates and facilitate their comparison.

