##### CPR Development

SHAP will be used to ‘translate’ model insights into CPRs. Mean—and not mean *absolute*—SHAP values will be used in order to preserve information on the directionality of feature importance. The decile rank of each of the eight mean SHAP values from each model will be calculated and a dot plot will be provided to visualise each feature’s mean SHAP value relative to others. (We speak of eight mean SHAP values because we have eight predictor variables corresponding to the features of CHA_2_DS_2_-VASc, namely five comorbid items, sex, and *two* age categories [65–74 years and ≥75 years]). The 25th, 50th, and 75th percentiles of the eight mean SHAP values will be computed. We will subsequently rank the features from most to least important and sort them into three tiers: (1) the lower tier grouping features with mean SHAP values below the 25th percentile, (2) the middle tier grouping features with mean SHAP values between the 25th and 75th percentiles, and (3) the upper tier grouping features with mean SHAP values above the 75th percentile. Features belonging to the lower, middle, and upper tiers will be assigned one, two, and three points, respectively. The purpose of a larger middle tier is to avoid over- or understating the importance of features by promoting stability over frequent changes with minor shifts in model parameters. In the rather unlikely event that one or more features will have negative mean SHAP values and local SHAP value distributions that are consistently left of zero on the beeswarm plots, zero points will be assigned, because their inclusion would degrade 90-day recurrence predictive performance. Ties at quantile cut-points will be resolved conservatively by assigning them to the higher category (e.g., features tied at the 75th percentile will enter the upper tier). The resulting CPRs will be summarised in tabular form and given an acronym in likeness to CHA_2_DS_2_-VASc.

If the dot plot suggests that the distribution of mean SHAP values is very skewed or concentrated, the above-defined tiers will probably inadequately capture features of lower, intermediate, and higher importance. In this eventuality, we will tailor tier boundaries using quantile-based binning. After adapting the tier setup to the observed clusters, we will define lower, middle, and upper tiers whose features will be assigned one, two, and three points, respectively.

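### The interaction cut is a percentile of the 28 values being judged, so for XGBoost and MLP it names two or three synergisms whatever their size or sign; their order against domain-knowledge pairs under the cap is not fixed

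*Protocol article*

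**What the plan says.** The section CPR Development works with eight features, "namely five comorbid items, sex, and *two* age categories". The section Global Interpretation counts the off-diagonal pairs, "28 of which are unique owing to the symmetry of SHAP interaction values". For each model the cut is then set from those values: "The 90th percentile of the sample of twenty-eight mean SHAP interaction values will be computed". The selection rule follows: "Feature-pairs with mean SHAP values above this threshold will be selected as the most important synergisms". Signed means are used rather than absolute means, so that synergistic pairs can be told apart from redundant ones.

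A second route admits pairs on domain knowledge, because "some feature-pairs have well-established synergisms that may merit inclusion even if they fall somewhat short of the 90th percentile cutoff". The three examples given are heart failure with age, hypertension with age, and hypertension with diabetes. Added points are capped at three, and so are pairs: "We will further cap the number of interaction pairs retained at a maximum of three".

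Table 3 (Analysis Plan column) describes the purpose of the step: "Interaction effects, captured through SHAP interaction values, will further refine our CPRs by identifying significant synergistic or redundant relationships between predictors". Plain and augmented rules are both evaluated afterwards.

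**The concern.** A percentile of the sample fixes how many pairs pass. It says nothing about how strong they are. The text adds no minimum size, no requirement that the value be positive, and no measure of uncertainty or stability, and it does not provide for the result that no pair qualifies. Main effects are treated differently: a feature whose SHAP values are consistently negative receives zero points. Interactions have no such exit.

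The augmented rules may therefore carry points that reflect noise, published under the name of synergisms, although Table 3 promises relationships that are significant and either synergistic or redundant. The cap raises a second problem. If the percentile route supplies three pairs, no place is left for a domain pair unless it displaces one of them, and no priority is stated. The choice is then open after the results are seen, in a protocol that presents prior planning as a safeguard against data dredging.

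**Working it through.** **Inputs.** Eight features and 28 pairs (Global Interpretation, CPR Development); 90th percentile, selection strictly above it, cap of three pairs (CPR Development); Python (Code Sharing); training set of 2072 (Sample Size and Power Analysis).

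**1. The plan's own count.** C(8,2) = 8 × 7 / 2 = 28. This reproduces.

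**2. How many pairs pass.** With Python's default linear interpolation, the 90th percentile of 28 ordered values lies at position 0.9 × (28 − 1) = 24.3, counting from 0. The values at positions 25, 26 and 27 lie above it, so exactly 3 pass. Over 13 percentile definitions with 3000 pure-noise draws each, the count was always 3 (nine definitions) or always 2 (four definitions).

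**3. Size and sign play no part.** Under the default definition:

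| 28 values | Pairs selected | Of these, positive |
|---|---|---|
| Noise of order 1e-9 | 3 | 3 |
| All negative | 3 | 0 |
| Two positive, 26 exactly zero | 2 | 2 |
| All exactly zero | 0 | 0 |

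The last two rows show the exception: heavy ties at the cut lower the count. If the rule for main-effect tiers, which sends ties to the higher category, were carried over, all 28 would qualify in both of those rows before the cap.

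**4. Data with no interaction.** In a logistic simulation, 200 data sets of 2072 patients were generated from main effects only. The assumptions, which are not figures from the protocol, were:
- feature prevalences of 20% to 65%;
- 25% of patients aged 65–74 and 55% aged 75 or over;
- an intercept of −2.2 and log odds ratios of 0.05 to 0.4.

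Fitted interaction coefficients stood in for SHAP interaction values, with the impossible age pair set to zero. The rule selected 3 pairs in 200 of 200 runs. On average 0.59 of the 3 had p < 0.05.

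**5. The cap.** Three selected pairs leave 3 − 3 = 0 places; definitions that select two leave 1. Because age enters as two categories, the three named examples are 2 + 2 + 1 = 5 pairs, which is more than the cap of three. If ranks were pure chance, the probability that none of the five is in the top three is C(23,3)/C(28,3) = 1771/3276 = 54%. In about half of such cases the domain route would matter only if displacement were allowed.

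**6. An impossible pair.** The 28 include age 65–74 with age 75 or over. No patient has both, so an accompanying rule for that pair could never apply, yet it could take one of the three places.

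**The case against.** The strongest reply is that naming candidate pairs settles nothing. CPR Evaluation compares plain and augmented rules on discrimination, calibration and net benefit. It adds a test tradeoff if an augmented rule ranks in the top three, and says that small differences favour the simpler rule. A reader might infer that the percentile rule forces a yes to Table 3's question on whether interactions improve prediction. The documents do not support that, because a negative answer remains available. The check is weaker than it looks, however: SHAP is summarised across the test set, CPR Development names no other data for the interaction values, and the rules are evaluated on that same set.

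A reader might also infer that every model always yields synergisms. For logistic regression no interaction terms are stated. On the log-odds scale its SHAP interaction values should all be zero, and a strict cut selects none, although rounding noise or SHAP on the probability scale could change that. Nor does the text say that domain pairs are blocked. It says that domain knowledge will also inform selection, some percentile definitions leave a place, and a named pair may already rank in the top three. What stands is that the order is not fixed in the article. Appendix S6, which is not shown, holds a worked example that may illustrate it.

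The use of signed means could be read as implying that negative pairs are not synergisms. That is a sensible reading, but the selection sentence does not require a positive value. The two caps limit how much noise can enter, not whether it enters.

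**Conclusion.** The point holds for XGBoost and MLP. Where the 28 values are distinct, the rule names 3 pairs (2 under some percentile definitions) as synergisms with certainty, whatever their size or sign. This follows from arithmetic and does not depend on the simulation, which only illustrates it under assumed prevalences and effects. The rule conflicts with the purpose of the signed means and with Table 3's description of the step. The consequence is confined to identifying interactions and building the augmented rules; the later comparison can still show no gain. Separately, the order between percentile pairs and domain pairs under the cap is not stated. No estimate of lost predictive performance is claimed.

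**What to change.** In CPR Development, replace the percentile cut with these rules:

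- Retain a pair only if its interaction value, computed in the training set, is positive and stable (for example, a bootstrap interval above zero), and adding the pair improves cross-validated log loss in the training set.
- State that zero pairs is an allowed result, in which case no augmented rule is built for that model.
- Exclude the pair of age 65–74 with age 75 or over, which leaves 27 candidates.
- State in advance the order between data-selected and domain-knowledge pairs under the cap. List the domain pairs by age category: the three named examples are five pairs and cannot all fit within three places.

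The form of the stability criterion is a matter of choice; what matters is that it is fixed before the analysis. The cost is a change of wording and bootstrap refits in the training set. The downside is that some models may yield no augmented rule.
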